### Recruitment

A letter and a poster will be distributed to psychiatrists at Providence Care Mental Health Services, informing them that they can refer clients to the CBTp Clinic, and they are invited to refer potential participants who meet an inclusion or exclusion criterion. Word of mouth and brochures or flyers will be prepared. The clinic staff or the participant will then contact our research coordinator or assistant to provide the potential participant with more information. The investigators plan to include individuals who are both inpatients and outpatients at Providence Care Hospital. This includes participants who may be in long-term care. Potential participants in the study will be referred to the CBTp Clinic at Providence Care Hospital by the participant’s primary treating psychiatrist.

During the first meeting at the CBTp Clinic, the potential participant will be informed about the study. The potential participant will be informed that their participation in the study is entirely optional, alongside the standard clinic disclosures about privacy/confidentiality. They will have the opportunity to consider further involvement in a study, with a break provided if they choose to meet with clinic personnel and provide written consent.

Express written consent to participate in the study will be obtained by a member of the research team who is not in the circle of care of the participant (at arm’s length).

### Participant Information and Informed Consent Procedures

Before data collection, potential participants will be fully informed of the observational nature of the study, in that the sponsor intends to collect information and follow the course of therapy in clinical practice. They will be told that their consent to allow the collection of information within the context of this noninterventional study is voluntary and may be withdrawn at any time. Only participants who are fully able to understand the nature of the research and provide their consent voluntarily will be enrolled. Participants must provide their informed consent after a comprehensive and understandable explanation of the clinical study’s nature, scope, and potential consequences. After reviewing the document, participants must give written consent. The consent process must be validated by the personally dated signatures of both the participant and the person facilitating the informed consent discussion. Participants will receive a copy of the signed consent document, while the investigator will keep the original. No study-specific procedures will be carried out until valid consent is obtained. If the participant agrees, their primary physician will be informed about their participation in the study. Where a participant has difficulty reading, a member of the research team will verbally communicate the information on a form or questionnaire if a participant requires clarification. Every effort will be made to help eligible participants with communication difficulties. In this study, the investigators do not enroll participants who are incapable of signing informed consent. To proactively monitor changes in the status of capacity, midway through the study, the research team will seek confirmation of the capacity status of the participant from health care personnel. As is typical ethical practice outside the scope of this study, if members of the CBTp Clinic (by way of observation or professional judgment) suspect a change in capacity in the participant, the participant’s primary treating psychiatrist will be notified, and a reassessment will take place.

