## Methods

### Trial Design

#### Description

This is a prospective, randomized, repeated-measures, single-blind study design. Preintervention, eligible participants will be randomly assigned to one of two treatment arms: arm 1 (tACS/CBTp, n=14) or arm 2 (sham tACS/CBTp, n=14; tACS is sham, but CBTp is active). In the intervention (16 weeks), participants in arms 1 and 2 will receive once-weekly tACS/CBTp or sham tACS/CBTp. Individuals with schizophrenia (*DSM-5* [*Diagnostic and Statistical Manual for Mental Disorders* {Fifth Edition} criteria) stratified by age and sex. The investigators expect 150 potentially eligible patients from Providence Care Mental Health Services, with 33-40 participants consenting to participate and 28 participants undergoing the research activities (see Figure 1).

Participants will be randomized 1:1 to one of two arms and stratified by age (18-30, 31-55, and >60 years) and by sex (male or female).

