#### tACS/Sham tACS

Participants randomized to the tACS arm will receive gamma band electric stimulation for 20 minutes at the beginning of each CBTp session. After the first 20 minutes of brain stimulation, the tACS device automatically stops, and the device remains in place while the CBTp session continues to run for 30 more minutes.

Participants randomized to the sham tACS arm will receive sham tACS for 20 minutes at the beginning of each CBTp session. After the first 20 minutes of sham tACS, the device automatically stops, and it remains in place, while the CBTp session continues to run for 30 more minutes.

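### Two sentences of the consent procedure call the study observational and noninterventional, which contradicts the randomised, sham-controlled trial described everywhere else

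*Protocol article*

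**What the plan says.** Under Participant Information and Informed Consent Procedures, the article opens with two sentences on what people hear before data collection. The first says that "potential participants will be fully informed of the observational nature of the study" and glosses this by adding that "the sponsor intends to collect information and follow the course of therapy in clinical practice". The second reads: "They will be told that their consent to allow the collection of information within the context of this noninterventional study is voluntary", with freedom to withdraw.

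The rest of the same section is of a different kind. It asks for a thorough and intelligible account of the study's character, extent and possible consequences before consent. It also requires signatures from both sides and allows no study procedure until consent is valid.

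The design sections describe an experiment. Trial Design, Description: "This is a prospective, randomized, repeated-measures, single-blind study design", and "Participants will be randomized 1:1 to one of two arms and stratified by age" and by sex. tACS/Sham tACS: "Participants randomized to the tACS arm will receive gamma band electric stimulation for 20 minutes at the beginning of each CBTp session", with a matching sham procedure in the other arm. Enrollment and Randomization says that only participants are blinded and that the arm is disclosed after the last follow-up visit or after withdrawal.

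**The concern.** An observational study records care that would have happened anyway. Here the study itself decides, by randomisation, whether a person receives active or sham stimulation, and withholds that information from them. The two labels and the gloss about following therapy in practice all point the same way, so this does not read as one misplaced word. Both sentences are framed as content to be conveyed to potential participants.

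The facts that such a description would leave out are ones the article itself treats as material. Risks of Participation says that the adverse effects of repeated tACS are not well understood, and that people in the sham arm may not improve. Limitations says that, to the authors' knowledge, the combination has not been used before in people with schizophrenia. The population includes inpatients and may include people in long-term care, and the consent section restricts enrolment to those able to understand what the research is. If the two sentences were carried into the operating documents, staff would have a direction at odds with that condition.

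**Working it through.** No calculation tests the contradiction. The check sets the texts side by side and then counts whom it could concern.

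**Side by side**

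| Feature | Opening of the consent section | Rest of the article |
|---|---|---|
| Study type | Observational; noninterventional | Prospective, randomised, single-blind (Trial Design, Description) |
| Who decides treatment | Nobody in the study; therapy is followed as it occurs in practice | Random allocation 1:1, stratified by age and sex (Description; Enrollment and Randomization) |
| What is given | Nothing; information is collected | Active or sham tACS with CBTp, 16 weekly sessions plus 2 boosters (tACS/Sham tACS; CBTp Intervention; Table 1) |
| Blinding | Not applicable to a study of that kind | Participants blinded (Enrollment and Randomization) |

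The descriptions conflict on every row.

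**Is it corrected elsewhere?** Three places come closest.

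1. The later sentence of the consent section asks for a full explanation. It does not withdraw the labels. A full explanation of this study would have to say that it is interventional, so the section gives two directions that cannot both be followed.
2. Ethical Considerations says that every participant receives a detailed, board-approved form explaining the study. It does not say how the form classifies the study.
3. Risks of Participation describes the sham group openly. That is consistent with the design sections and inconsistent with the two sentences.

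None of these reconciles the wording.

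**Whom it could concern.** Table 2 places consent at visit 1, and Enrollment and Randomization places randomisation after the screening visit. The relevant count is therefore people consented, not people randomised or treated.

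- Planned: the Description section expects 33 to 40 to consent, of whom 28 go on to the research activities. The planned count is 33 to 40.
- To date: the abstract reports 15 enrolled by 1 November 2025, made up of 12 in the intervention (8 active + 4 sham), 2 screening failures and 1 withdrawal after the second session; 12 + 2 + 1 = 15. Leaving out the screening failures gives 15 − 2 = 13. But screening failures are identified at or after the visit where consent is taken, so presumably all 15 consented.

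**Effect on the statistics.** The two sentences enter no endpoint, allocation rule or analysis. Sample size, alpha and power do not change.

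**The case against.** The strongest reply is that these are two sentences in a journal article, not the document used with participants. Consent is taken on a board-approved form, and monitoring is against the board-approved protocol; neither is shown. The consent section does more than describe data collection, since it also demands a full explanation. The risk section, the rules on disclosing the arm and the planned debriefing letter all suggest, without proving it, that participants know a sham arm exists.

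Most of this stands, and it limits the finding. A reader might infer that every participant has been misinformed, that consent omitted randomisation and sham, or that the collected data may be unusable. The documents support none of these. All three depend on the content of a form that is not available, and the last has no link to any endpoint or analysis.

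The reply does not remove the contradiction. Condensing a protocol for a journal explains what is left out; it does not explain a positive statement that the study is something it is not. If the form is accurate, the article conflicts with it and needs correcting. If the form carries the same wording, the problem is larger. The two sentences have to change in either case.

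**Conclusion.** The point holds as an internal inconsistency. Two sentences presented as what participants will be told are wrong for this trial. They contradict the design, allocation, intervention and blinding sections, and they conflict with a requirement in their own section. Because this is the stated consent procedure for a vulnerable population and the correction is nearly free, it should be made.

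Its size is limited to the wording. Whether it reached participants is unknown. If it did, the people concerned are those who consented: presumably 15 by 1 November 2025, and 33 to 40 over the trial. The figure of 15 assumes that the two screening failures signed consent at visit 1, as Table 2 implies. The check does not rest on any figure for effect, variance or dropout.

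**What to change.** - Replace the two sentences with a plain statement that this is a randomised, sham-controlled, participant-blinded interventional trial, in which people are allocated 1:1 to active or sham tACS alongside CBTp.
- Check that the approved protocol, the consent form and any scripts in use contain neither *observational* nor *noninterventional* as a description of the study.
- Only if one of them does, take it to the ethics board for everyone already consented, including those who failed screening.

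The cost is two sentences and one check of existing documents. No change to the design, sample size or analysis follows.

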### Reimbursement

The investigators will provide each participant with a US $10 reimbursement to cover out-of-pocket expenses, such as a snack and bus ticket, for each of the 6 required visits as part of the study. Payments will be provided after each task is complete. Participants will be encouraged to bring a lunch with them, as indicated on the informed consent form.

### Enrollment and Randomization

After the screening visit, participants will be randomized in a 1:1 ratio with stratification according to age and sex.

Maintaining the blind is covered by the device, which induces a discrete tickling sensation at the starting point of the intervention for participants on sham tACS. This study is single blind, being blinded only for participants. In case of emergency, the research team would be aware of the interventional (or sham) nature of the problem. Communication with participants regarding this aspect will be possible only at the end of the study, at the end of visit 6 (second follow-up), at the patient’s request, or after they withdraw from the study. At the study closure, each participant will receive a debriefing letter containing unblinding disclosure.

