**Methods:**

This is a pilot, prospective, randomized, repeated-measures, single-blind study design. We expect to enroll 28 participants randomly assigned to one of two treatment arms: arm 1 (tACS/CBTp, n=14) or arm 2 (sham tACS/CBTp, n=14; tACS is sham, but CBTp is active). The intervention with active or sham tACS/CBTp will take place weekly for 16 weeks. Primary outcome measures—electroencephalogram, Positive and Negative Syndrome Scale, 16-item Negative Symptom Assessment, and Cognitive Flexibility Scale—will evaluate the efficacy of treatment at the end of the intervention and at the two follow-ups. We will use SPSS (version 29, IBM Corp); the main tests will include repeated measures and mixed design ANOVA.

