### Statistical Outcomes

#### Primary Outcome Measures

EEG gamma oscillations are fast neural rhythms linked to higher-order cognitive functions (attention, working memory, executive control, and consciousness). In the prefrontal cortex, gamma EEG activity is associated with working memory maintenance, cognitive flexibility, top-down attention control, and integrating information across cortical areas. Altered prefrontal gamma observed in schizophrenia. EEG measurement of gamma activity in the prefrontal cortex refers to detecting brain oscillations in the gamma frequency band (typically 30-100 Hz, often subdivided into low gamma: 30-50 Hz, and high gamma: 60-100 Hz) from scalp electrodes positioned over prefrontal areas. In a within-subject design, we will compare gamma power across time windows (pre- and postintervention). In a between-subject design, we use mixed models or *t* tests on summary metrics (mean power in time×freq window).

PANSS is a standardized clinical interview that rates the presence and severity of positive and negative symptoms and general psychopathology for people with schizophrenia within the past week [32]. The scale consists of 30 items: 7 positive, 7 negative, and 16 general psychopathology symptoms. The symptom severity for each item is rated according to a 7-point scale (1=absent to 7=extreme) to best describe the symptom’s presentation. The clinical interview takes approximately 45 minutes. The patient is rated from 1 to 7 on 30 different symptoms based on the discussion and reports of family members or primary care hospital workers. As 1 is the lowest score for each item, a patient cannot score lower than 30 for the total PANSS score. Scores are often given separately for positive items, negative items, and general psychopathology. [Time frame: PANSS will be applied at visit 1, screening (week 0); visit 4, end of intervention (week 17); visit 5, follow-up 1 (week 21); and visit 6, follow-up 2 (week 29).]

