### Privacy and Confidentiality

Participant names will remain confidential and not be disclosed to those not involved in the study. In the CRF, only the participant number will be recorded. If any identifiers appear on any document, they will be redacted in copies stored in the site master file or presented for audit. Data stored electronically will comply with local data protection laws. Participants will be informed that ethics committees or research ethics boards may inspect their records and that all personal information will be treated with utmost confidentiality in line with local data protection laws. The investigator will keep a list linking participant numbers to names for record identification and retrieval.

EEG sample recordings will be stored in a file on the designated laptop, where they will remain anonymous, identified only by a code number. Postrecording, the samples will be transferred to a secure server at Queen’s University, anonymized, and then deleted from the original recorder. These anonymized files will be stored on the server for 15 years after data collection ends, after which they will be permanently deleted.

Any chart reviews will be conducted by hospital-appointed individuals who have the privilege to access them.

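### Blinding stops at the participant, so EEG processing, the choice of gamma band, window and test, and the analysis are not masked to arm

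*Protocol article*

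**What the plan says.** Enrollment and Randomization restricts masking in so many words: "This study is single blind, being blinded only for participants". The next sentence adds: "In case of emergency, the research team would be aware of the interventional (or sham) nature of the problem". No section names a masked assessor, EEG processor or analyst.

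The abstract lists four primary outcomes: "Primary outcome measures—electroencephalogram, Positive and Negative Syndrome Scale, 16-item Negative Symptom Assessment, and Cognitive Flexibility Scale". For EEG, Primary Outcome Measures describes the gamma band as "typically 30-100 Hz, often subdivided into low gamma: 30-50 Hz, and high gamma: 60-100 Hz" and does not say which range is primary. For the between-arm comparison it states: "we use mixed models or *t* tests on summary metrics (mean power in time×freq window". The window is not given.

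Privacy and Confidentiality says: "EEG sample recordings will be stored in a file on the designated laptop, where they will remain anonymous, identified only by a code number". Study Oversight and Data Management leaves the list that links codes to identities with the principal investigator or a delegate.

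Statistical Considerations: Sample Size makes unbiased estimates of the standard deviation and preliminary effect sizes one goal of the pilot, and calls the outcome analyses descriptive, with 95% CIs.

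**The concern.** Prefrontal gamma power comes out of a chain of judgements: which segments to reject, which band to average over, which window to use. If those judgements are made by people who know the arm, chance differences can be turned into an apparent advantage for one arm. The team states in the abstract and in Objectives that it expects active tACS to do better, so the direction of any such pull is known.

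What is at stake is the pilot's own product. An effect size inflated by arm-aware choices would feed the planning of the definitive trial. The Disseminations section also plans a funding application from preliminary or interim analysis. Labelling the analyses descriptive does not help, because the bias sits in the estimate itself and not only in a p value.

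**Working it through.** **1. The plan's own figure.** The sample-size section gives a minimal detectable effect of about d = 1.1 with 14 per group. Alpha and power are not stated; I assume two-sided 0.05 and 80%.
- Normal approximation: (1.960 + 0.842) × √(2/14) = 2.802 × 0.378 = 1.059.
- Noncentral t: 1.100.

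The figure reproduces and is not in dispute. It also gives the scale: the standard error of d near zero is about √(2/14) = 0.378.

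**2. Does any section mask EEG processing or analysis?**
- Enrollment and Randomization says only participants are blinded. This is an explicit restriction, not silence.
- The code numbers in Privacy and Confidentiality and the restricted identifier list protect identity. Neither is said to hide the arm.
- Monitoring Plan has the monitor check that the blind is maintained, but the blind in question is the participants'.

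Masked processing is therefore not part of the plan as written, and a later document that added it would conflict with the word limiting the blind to participants.

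**3. What an arm-aware choice of band could do.** Inputs: 14 per arm (sample-size section); k = 3 candidate bands, namely 30-100, 30-50 and 60-100 Hz (Primary Outcome Measures); no true effect; equal correlation ρ between the band measures. The value of ρ is an assumption, so a range is shown. The analyst keeps the band with the largest d in favour of active tACS.

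Expected spurious d ≈ √(1 − ρ) × E[max of 3 standard normals] × √(2/14) × small-sample factor, where
- E[max of 3] = 3/(2√π) = 0.846,
- small-sample factor = 1/(1 − 3/(4×26 − 1)) = 1.03, with 26 degrees of freedom.

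| ρ | Calculation | Formula | Simulation |
|---|---|---|---|
| 0.5 | 0.707 × 0.846 × 0.378 × 1.03 | 0.23 | 0.23 |
| 0.7 | 0.548 × 0.846 × 0.378 × 1.03 | 0.18 | 0.18 |
| 0.9 | 0.316 × 0.846 × 0.378 × 1.03 | 0.10 | 0.10 |

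Relative to the standard error this is 0.10/0.378 ≈ 0.3 to 0.23/0.378 ≈ 0.6 standard errors, always towards active tACS. With one band fixed in advance, or chosen without knowledge of the arm, the expected shift is zero.

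**4. Which calculation speaks to blinding.** Taking the smallest two-sided p among several bands also raises the false-positive rate; for three bands it is about 12% at ρ = 0.5. That result does not change if the arm labels are swapped, and the mean selected d stays at zero. It measures lack of prespecification, which masking would not cure. Only the directional calculation in step 3 depends on knowing the arm.

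**The case against.** The case against has several parts.

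- **The person cleaning the files may not know the arm.** The article mentions team awareness in the context of emergencies, files carry codes, and participants are blinded at recording. This stands as far as it goes: knowledge of the arm is not shown for any particular person. But nothing in the plan withholds it, and the blinding sentence excludes everyone except participants.
- **Band, window and artefact rules normally sit in the SAP or an EEG manual.** This also stands. Their absence from a journal article is not the point here, and they may already be fixed elsewhere. The point is the explicit limit on blinding, combined with the alternatives the article does print. The article is not wholly open either: electrodes are prefrontal, and Table 2 has EEG only at visits 1 and 4.
- **PANSS and NSA-16 are more directly exposed.** They are rated by people not stated to be masked. This is true, but it adds to the problem and does not remove it for EEG.
- **The trial is descriptive.** This makes a false-positive rate a poor yardstick. It does not excuse bias in effect sizes that are meant to be unbiased.

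Two stronger readings are tempting and not supported. A reader might infer that EEG is the one primary outcome needing no rater. The CFS is a 12-item agree/disagree scale that appears to be self-completed by blinded participants, so EEG is only the sole physiological primary outcome. A reader might also infer that EEG has lost its protection from bias. The participant blind still covers the recording; what is missing is any stated masking after it.

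**Conclusion.** The point holds as an opportunity for bias. The plan limits blinding to participants, masks neither EEG processing nor analysis, and prints more than one band and test for a primary outcome. If the most favourable of the three printed bands were chosen with the arm known, the expected spurious d in favour of active tACS would be about 0.10 to 0.23 under no true effect.

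This rests on 14 per arm, three candidate bands with equal correlation between 0.5 and 0.9, and a deliberately favourable choice. The correlation is assumed; the full band contains the two sub-bands, so equal correlation is a simplification. Freedom over windows or artefact rejection is not included. Nothing in the documents shows that such choices have been made, and inflated false-positive rates from trying several windows should not be cited as evidence about blinding. The change is worth making because it is cheap and protects a stated goal of the pilot.

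**What to change.** Amend Enrollment and Randomization and the EEG paragraph of Primary Outcome Measures to say that:

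1. an existing team member without access to the allocation list processes the code-numbered EEG files;
2. artefact rules, one primary gamma band and window, and one between-arm test are fixed on arm-masked files before the allocation key is joined, with any other band reported as supportive;
3. the analysis is run first with arms labelled A and B, and the key is joined afterwards.

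Staff who deliver stimulation can go on knowing the arm. With 12 participants following the intervention protocol at the last report, this can be adopted before the final analysis.

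The cost is a paragraph of protocol wording and separation of tasks within a small team. The article does not show who is free of session duties and has no access to the allocation list, so the team should confirm that such a person is available.
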